## Abstract

**Background:**

In children with early-onset anorexia nervosa (first symptoms before 13 years old, EO-AN), experts recommend initial outpatient treatment but in-patient treatment (IP) is frequently indicated due to acute medical instability or for those who have not improved with outpatient treatment. This IP can target either a partial weight restauration or a total weight normalization (return to the previous BMI growth trajectory). There are no evidence in the literature on which is the better therapeutic option in EOAN. But as long length of stay induce social isolation, with elevated costs, we wonder if a stepped-care model of daypatient treatment (DP) after short IP stabilisation may be a treatment option as effective as full-time IP to target weight normalization. We designed a two-arm randomised controlled trial testing the non-inferiority of a stepped-care model of DP after short IP stabilisation versus full-time IP.

**Methods:**

Eighty-eight children aged 8 to 13 years suffering from EOAN with initial severe undernutrition will be randomly allocated to either IP treatment as usual or a stepped care DP model both targeting weight normalization. Assessments will be conducted at inclusion, somatic stabilization, weight normalization, 6 months and 12 months post randomisation. The primary outcome will be BMI at 12 months post-randomisation. Secondaries outcomes will included clinical (tanner stage), biological (prealbumin, leptin, total ghrelin and IGF1) and radiological (bone mineralization and maturation) outcomes*,* eating symptomatology and psychiatric assessments, motivation to change, treatment acceptability and quality of life assessments, cost-utility and cost-effectiveness analyses.

**Discussion:**

COTIDEA will provide rigorous evaluation of treatment alternative to full-time inpatient treatment to allow a reduction of social iatrogenic link to hospital length of stay and associated costs.

**Trial registration:**

Trial is registered on ClinicalTrials.gov (NCT04479683).

## Background

Early-onset anorexia nervosa (EOAN) is characterised by disease onset in children before the age of 13 years old and will thus include prepubertal and post pubertal onset [1]. Compared to the classic adolescent form of anorexia nervosa (AN), EOAN presents clinical and epidemiological specificities [1]. Children with EOAN more often present severe restrictive forms with more rapid weight loss, associated with a greater frequency of total aphagia and the presence of associated "non-specific" somatic symptoms (digestive complaints, abdominal pain) [2–4]. Frequently requiring inpatient treatment, children with EOAN also have a higher average length of stay (LOS) than adolescents with AN [1]. Despite an increased prevalence [5] and a specific burden in pediatrics and mental health departments, treatment knowledge remains sparse, and based on mainstream clinical opinion with little empirical standing [6]. In clinical practice, in children with AN, whereas experts recommend outpatient treatment (OP), in-patient treatment (IP) remains frequently indicated due to acute medical instability [6] or for those who have not improved with OP. Long LOS, social isolation, and elevated costs have led to discuss different treatment options with age-appropriate strategies for child population [6, 7].

In recent years, in adolescents with a mean age of 15 years old, day patient treatment (DP) following initial IP has been developed [8, 9]. Results support comparable efficacy, better acceptability and lower cost in the management of moderate AN, compared to prolonged IP, but also better social adjustment and more age-adequate autonomy [6, 8]. A Cochrane meta-analysis reports no difference between specialised full-time IP compared to combined brief IP and OP in weight gain at 12 months follow-up [10]. Similar clinical and cost effectiveness evaluations are currently conducted in adult AN population to compare IP to combined IP/DP [11]. Rigorous assessment of this treatments approaches is necessary to adapt national and international guidelines. Particularly, replication of randomised controlled trial focusing on younger populations under 13 years old is needed to test alternative care modalities to extended IP. In children aged 8–13 years with EOAN, somatic condition frequently requires continuous inpatient monitoring [1], DP cannot initially be proposed. We wonder if we could shorten the duration of IP by relaying care in a one day a week DP after somatic stabilisation, with a comparable effectiveness in weight gain and maintenance, a better acceptability, a better evolution in terms of school and friendship integration, and a lower cost.

COTIDEA trial aims to compare a stepped-care model of DP after short IP stabilisation to full-time IP in a two-arm open-label, single centre, non-inferiority randomised controlled trial in children and adolescents under 14 years old with EOAN and initial severe undernutrition.

The specific objectives of the propose study are to:

Demonstrate non-inferiority of a stepped-care model of DP after short IP stabilisation versus full-time IP based on BMI at 12 months post-randomisation (primary outcome).Demonstrate non-inferiority of a stepped-care model of DP after short IP stabilisation in term of clinical, biological outcomes, AN symptoms, comorbidities, and relapse at different time points (weight normalization, 6, 12 months).Assess the impact of a stepped-care model of DP after short IP stabilisation versus full-time IP on treatment satisfaction and quality of life of patients and parents at 6 and 12 months.Assess the impact of the prospect of discharge to DP on initial IP (duration before somatic stabilisation, motivation to change) at inclusion and somatic stabilisation.Determine factors associated with positive response to stepped-care model of DP after short IP.Determine the cost-utility and cost-effectiveness of a stepped-care model of DP after short IP stabilisation compared with full-time IP.

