### Data analysis

#### Sample size

We calculated the sample size for a one-sided Student’s t test with a significance level of 2.5% and a power of 90% based on the clinically determined non-inferiority margin for a difference in BMI of 1 kg/m2, assuming a distribution of the BMI of 16,6 ± 1,35 kg/m^2^. This procedure led to a required sample size of 80 patients (40 per group). Assuming a dropout rate of 10% [8], we calculated a sample size of 88 patients. We aim to include 88 children with EOAN (44 per group).

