#### Statistical analysis plan

The statistical analysis of the data will be performed using an intention-to-treat analysis, all patients allocated to the control group or experimental group will be analysed. The descriptive analysis for each group at each assessment time will be expressed as number (percentage) for categorical variables, and as mean (SD) or Median [IQR] according to their normal or non-normal distribution for quantitative variables. As described above, the primary outcome for non-inferiority analysis is based on the comparison of the BMI at 1 year after inclusion between the two groups with a two-sided 95% confidence interval. Experimental strategy will be considered as non-inferior if the confidence interval upper limit of the difference in BMI between the 2 groups is less than 1 kg/m^2^ (non-inferiority margin) with a 0.025 alpha risk. The comparative analysis between the 2 groups for the primary or secondary criteria will be carried out using the appropriate tests: Chi^2^ test or Fisher's exact test for qualitative variables; Student's t test or non-parametric Wilcoxon test for quantitative variables, according to their normal or non-normal distribution. To determine prognosis factors associated with positive response to stepped-care model of DP after short IP, a regression model will be used to search for factors associated with the effect of the intervention, integrating the MRS score as the explained variable, and the CGI score, the HAQ11 and motivation questionnaire scores, and the severity of the weight deficit as explanatory variables.

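### The second objective claims non-inferiority on secondary outcomes, but the tests stated for them cannot show it

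*Protocol article*

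**What the plan says.** The Background of the protocol article lists six specific objectives. The first is non-inferiority on BMI at 12 months. The second uses the same verb for a wide set of other outcomes: "Demonstrate non-inferiority of a stepped-care model of DP after short IP stabilisation in term of clinical, biological outcomes, AN symptoms, comorbidities" and relapse, at weight normalisation, 6 months and 12 months. The third and fourth objectives are softer and speak only of assessing impact.

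The Sample size section rests on one margin, the "clinically determined non-inferiority margin for a difference in BMI of 1 kg/m2". The Statistical analysis plan section turns it into a decision rule for BMI at one year, based on a two-sided 95% confidence interval. Non-inferiority is concluded if the "confidence interval upper limit of the difference in BMI between the 2 groups is less than 1 kg/m^2^ (non-inferiority margin").

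The same section then gives the method for everything else: "The comparative analysis between the 2 groups for the primary or secondary criteria will be carried out using the appropriate tests". The tests are Chi-square or Fisher's for categorical variables and, for continuous ones, Student's "t test or non-parametric Wilcoxon test for quantitative variables, according to their normal or non-normal distribution". No non-inferiority criterion is attached to any secondary outcome there or in the Measures section.

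**The concern.** In their usual form the listed tests take no difference as the null hypothesis. Rejecting that null shows that the arms differ. Failing to reject it shows neither that they are alike nor that one is acceptably close to the other. To show non-inferiority, a confidence limit must be compared with a margin, or a null shifted by that margin must be tested. The document does this for BMI at 12 months and for nothing else.

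The second objective is therefore paired with a method that cannot answer it. The only way those tests could appear to satisfy it is for a non-significant p-value to be taken as evidence of no inferiority. That reading would favour the experimental arm, because measurement noise and loss to follow-up both make non-significance more likely. The outcomes concerned include eating symptoms, comorbidities and relapse in children aged 8 to 13, and the Background presents trials of this kind as input to treatment guidelines.

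**Working it through.** **Inputs from the protocol article, Sample size section.** Margin 1 kg/m², SD 1.35 kg/m², one-sided alpha 0.025, power 90%, 40 per group, 10% dropout, 88 in total.

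**1. Reproducing the stated size.** The BMI margin in SD units is 1/1.35 = 0.741. With n per arm and no true difference, the t statistic against the margin has noncentrality 0.741 × √(n/2) on 2n − 2 degrees of freedom. At n = 40 this is 0.741 × √20 = 3.31 on 78 degrees of freedom, and power is 90.5%. At n = 39 power is 89.8%. So 40 per arm, 80 in all, is reproduced, and 80 × 1.1 = 88. The size is sound for the primary comparison and rests on the BMI margin alone.

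**2. How often a difference test misses a true deficit.** The documents give no SDs or expected effects for the secondary outcomes, so the standardised deficits d below are assumptions. For a two-sided 5% t test with 40 per arm, the critical value on 78 degrees of freedom is 1.991 and the noncentrality is d × √20.

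| Assumed true deficit d (SD) | Noncentrality | Power | Probability of non-significance |
|---|---|---|---|
| 0.3 | 1.34 | 0.263 | 74% |
| 0.4 | 1.79 | 0.424 | 58% |
| 0.5 | 2.24 | 0.598 | 40% |

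**3. A binary outcome.** Relapse rates are not given either. Taking 20% against 35% as an assumption, Fisher's exact test with 40 per arm has power 0.245, so it is non-significant about 75% of the time.

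**4. What the interval could exclude.** The half-width of a 95% CI for a mean difference is 1.991 × √(2/40) = 0.445 SD. An observed difference of zero would leave deficits of up to about 0.45 SD compatible with the data.

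**5. What a proper non-inferiority test could do at this size.** With no true difference and 40 per arm, power is 26% for an assumed margin of 0.3 SD and 60% for 0.5 SD. It reaches about 90% only near 0.74 SD, the primary margin in SD units.

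**The case against.** Four points can be made for the plan.

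- **No such reading is stated.** A reader might infer that the investigators intend to read p > 0.05 as non-inferior. No sentence in the document says so. This stands in full: the misreading is a risk created by pairing this objective with these tests, not a stated rule.
- **Margins may be held elsewhere.** A reader might also count the missing secondary margins as a fault in themselves. This is a journal article that cites a protocol version not shown, and an analysis plan may exist. Margins for individual secondary outcomes are commonly left to such documents, so their absence here is no finding. What remains is that the article does name a method for the secondary criteria, and it does not fit the objective.
- **The test list is generic.** The sentence covers primary and secondary criteria alike, and for the primary outcome it sits beside a margin rule. The Sample size section also uses a one-sided Student's t test for a non-inferiority comparison. Naming a t test therefore does not by itself exclude an analysis against a margin. This is fair but limited: no such rule is written for the secondary outcomes, and Chi-square, Fisher and Wilcoxon as normally used are difference tests. The BMI margin could at most be carried over to BMI at other visits. It has no meaning for the symptom scales, the hormones or relapse.
- **The figures are generic.** They describe any trial with 40 per arm under assumed effects. That is true. They show the size of the risk and are not evidence of an error in the trial's own calculations.

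**Conclusion.** The mismatch is real: the document commits itself to demonstrating non-inferiority on a broad set of secondary outcomes and states for them tests that, as listed, cannot do so. Under assumed true deficits of 0.3 to 0.5 SD and 40 evaluable patients per arm, between 74% and 40% of trials would give a non-significant t test. A null result on these outcomes would thus say little about whether the day-patient strategy is acceptably close to full-time inpatient care.

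A reader might conclude that the trial's non-inferiority claim as a whole is undermined. The documents do not support that: the primary comparison has its own margin, interval rule, alpha and a sample size that reproduces. The point should be fixed, but it concerns the secondary claims only.

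**What to change.** - Reword the second objective as estimating the difference between the two strategies on the listed outcomes.
- In the Statistical analysis plan section, report each secondary outcome as an arm difference with a 95% CI.
- State that no non-inferiority conclusion will be drawn from a non-significant test.
- If any secondary outcome is to keep a non-inferiority claim, name it and judge it by its CI against a margin justified and fixed before data are seen. If the full protocol or analysis plan already holds such margins, the article's text should be brought into line with them.

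The cost is a change of wording in one objective and in the analysis section. The trial gives up secondary non-inferiority claims that the stated tests could not have supported. The primary analysis, sample size, visits and treatment are unchanged.

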### Procedure (Fig. 1)

**Fig. 1 Fig1:**
[figure not shown]
Study flowchart

At initial clinical assessment, eligible children and caregivers will be informed of the study and study protocol is fully explained by the investigator. After signature of the informed consent by the holder(s) of parental authority, target weight for weight normalisation will be calculated and participants will be randomised into one of the two trial arms. Weight normalisation is individualised and will be determined at inclusion and before randomisation to return to the previous BMI growth trajectory and is calculated by two different investigators [15–18].

Randomisation will be done by a randomisation list with the nQuery Advisor and nTerim 4.0 software implemented in the eCRF. Children and parents are informed of the result of the randomisation by the investigator.

After inclusion and randomisation, participants will be managed in 3 phases:

*period 1: *Full-time IP until somatic stabilisation (see below for definition); *period 2:* DP or IP according to their randomisation arm until weight normalisation is reached; *period 3:* OP follow-up.

*Period 1: *Full-time IP—identical for all included children- ongoing until somatic stabilisation, which is defined as: BMI over the 3^rd^ percentile, disappearance of somatic severity criteria for undernutrition such as bradycardia (heart rate below 40 per minute during sleep time or below 50 per minutes during day time), persistent disturbances of the biological balance (hypoglycaemia, hypophosphoremia, haemolysis, cytolytic hepatitis, elevated creatine kinase), or any somatic or biological manifestation requiring constant surveillance in hospital with usual medical, dietary and psychological care (persistent refusal to drink or eat, lipothemia, hypothermia). The treatment provides multi-disciplinary care for the child and his/her family as described in French guidelines [14], including:Child follow-up of AN and psychiatric comorbidities by a senior psychiatrist on a bi-weekly basisEndocrinologic and somatic evaluation by a senior endocrinologic paediatric for initial assessment M6 and M12 and by a psychiatrist resident for follow-up during IP and by a general practitioner during OPNutritional monitoring with a bi-weekly dietetic follow-upPsychological follow-up with weekly family therapyTherapeutic education for the child with a weekly psychoeducation group and day-care nurse follow-up

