We will target a rapid weight gain from 500g to 1.5kg a week depending on the tolerance [19].

*Period 2: *At the end of the first period, patients start to receive treatment according to their randomisation arm until the weight normalization is reached. *For the control group*, full-time IP is continued as described in period 1 with additional cognitive remediation weekly group and weekly individual cognitive-based therapy until the weight normalisation is reached. During this time period, IP patients can benefit from permission to go home twice a week on Wednesday afternoons and weekends. *For the experimental group*, participants are discharged from IP and switch to DP one day per week until weight normalisation is reached.

The standardized DP treatment combines a medical assessment by a senior psychiatrist, family oriented treatment (parents' group and multi-family therapy session), a psychoeducation group, a cognitive remediation group, a dietetic follow-up with therapeutic meals and body constants monitoring (heart rate and blood pressure). Patients in the experimental group can return to their school activities and home life. During this period, the number of individual cognitive-based therapy sessions out from the hospital will be reported. If absence of weight gain leading to a BMI < 3rd percentile or weight loss of more than 10% of body weight during DP, patient will be readmitted to full-time IP until the weight normalisation is reached.

*Period 3: *After weight normalisation is reached, all patients will be provided the same OP follow-up until 12 month with a psychiatric consultation every month for 3 months and then once every 2/3 months as proposed in usual care.

Clinical, biological and psychometric assessments are done at baseline, at somatic stabilisation, at reaching weight normalisation, at 6 months and 12 months following study inclusion.

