#### Secondary outcomes

*Biological and radiological outcomes* will be collected. *Nutritional status* will be assessed with prealbumin, leptin, total ghrelin and IGF1. Body composition and *bone mineralisation* will be estimated by using dual-energy X-ray absorptiometry (DEXA, GE Lunar ProdigyCorp., Madison. WI). Bone mineral measurements will be expressed as standard deviation score according to age and sex (SDS). *Bone maturation* will be assessed from an en face radiograph of the left wrist, interpreted using the Greulich and Pyle atlas.

*Global clinical and psychological evaluation* will be assessed with the *Clinical Global Impression* (CGI) [20] scale. CGI is scored on a two-part 7 response levels evaluating illness severity (CGI-S) and improvement (CGI-I) from 1 (“not ill”/ “very much improved”) to 7 (“extremely ill”/ “much worse”).

*Eating disorder symptomatology* will be assessed with the *Morgan and Russell scale* (MRS) [21] and the *Children Eating Disorders Inventory* (EDI-c) [22, 23]. The MRS is a questionnaire designed to evaluate the long-term evolution of the eating disorder and is used to assess the main aspects of anorexia nervosa over a six-month period. A version has been adapted for younger children, with deletion of non-appropriated items as "menstruation", "psychosexual functioning" and "emancipation". The assessment of the adapted procedure has 8 subscales divided into 3 groups: Eating; Mental status; Socioeconomic Status.

The EDI-c is adapted form of the EDI for children from 8 years of age onwards [22, 23]. This is a multidimensional self-questionnaire that assesses different psychological, behavioural and emotional characteristics associated with eating disorder symptoms. It comprises 91 items divided into 11 factors: Drive for Thinness, Bulimia, Body Dissatisfaction, Low Self-Esteem, Personal Alienation, Interpersonal Insecurity, Interpersonal Alienation, Interoceptive Deficits, Emotional Dysregulation, Perfectionism, Asceticism, and Maturity Fears. Each of the 91 items is rated from 'never' to 'always', respectively from 0 to 3 for direct items and from 3 to 0 for indirect items.

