*Quality of life* will be assessed by the *Short-Form 12-Item Health Survey* (SF-12) [29, 30]. The SF-12 is a generic self-assessment scale of quality of life and a shortened version of the SF-36 validated in France. It contains 12 questions. It provides two scores: a physical health and a mental health summary scores. These two scores were constructed so that their average in the general population is 50 and range from 0 to 100, 100 indicating the highest level of quality of life.

*Social functioning* will be particularly evaluated based on the subscales of the MRS assessing the socioeconomic status: relationship with family, social contacts outside family, social activities and scolarity.

*Direct and indirect costs* will be calculated from resources consumption: all hospital admissions will be recorded as ambulatory consultations, complementary examinations, medical transport and number of non-working days for parents due to medical care for their child for control and experimental groups will be recorded.

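### Objective 2 tests non-inferiority at the weight-normalisation visit, which is triggered by reaching target weight, so the comparison there says little about weight, is not ITT and can hide slower recovery

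*Protocol article*

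**What the plan says.** All references are to the protocol article.

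- **Background, second specific objective.** Non-inferiority is to be demonstrated on clinical and biological outcomes, anorexia symptoms, comorbidities and relapse "at different time points (weight normalization, 6, 12 months".
- **Procedure, target.** "Weight normalisation is individualised and will be determined at inclusion and before randomisation to return to the previous BMI growth trajectory".
- **Procedure, period 2.** Treatment is "DP or IP according to their randomisation arm until weight normalisation is reached". In the experimental arm, if day care fails by the stated criteria, the "patient will be readmitted to full-time IP until the weight normalisation is reached".
- **Procedure, schedule.** Assessments take place "at baseline, at somatic stabilisation, at reaching weight normalisation, at 6 months and 12 months following study inclusion". Two of the five are therefore triggered by events.
- **Table 1.** BMI, nutritional markers, CGI, EDI-c, MRS, CDI, STAIC, Rosenberg, HAQ-11S, motivation, CSQ-8 and SF-12 are all collected at weight normalisation. Nutritional markers are not scheduled at 6 months.
- **Secondary outcomes.** The MRS is "used to assess the main aspects of anorexia nervosa over a six-month period". Social functioning "will be particularly evaluated based on the subscales of the MRS assessing the socioeconomic status".
- **Statistical analysis plan section.** The analysis is by intention to treat, with every allocated patient analysed. Secondary criteria are compared between arms with ordinary two-group tests.

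**The concern.** A between-arm comparison needs a time that treatment cannot move. This visit occurs when the child's weight reaches target, and the two treatments differ in the phase leading up to it. Four consequences follow.

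1. BMI at the visit is roughly the pre-randomisation target in both arms, so it cannot show that one arm restored weight more slowly.
2. Relapse is listed at this time point, but relapse after normalisation cannot yet have happened.
3. A slower arm would be assessed later, after more therapy and more growth, and the delay would not appear in the result.
4. A child who never reaches target contributes nothing, which departs from the stated analysis of all allocated patients.

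The MRS has a further problem. At a visit before month 6, its six-month window reaches back before randomisation, when the arms cannot differ because of treatment. This dilution favours a finding of non-inferiority. At stake is a published statement of non-inferiority at a time point that could not have revealed inferior weight restoration.

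**Working it through.** **Step 1. The plan's own figure.** Inputs from the Sample size section: margin 1 kg/m², SD 1.35, one-sided alpha 2.5%, power 90%, true difference 0.
n per arm = 2 × (1.960 + 1.282)² × 1.35² / 1² = 38.3, so 39. The exact noncentral t gives 89.8% power at 39 per arm and 90.5% at 40. The stated 40 per group reproduces. The present point does not depend on it.

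**Step 2. BMI at the visit.** For each child, BMI at the visit = target BMI + overshoot + effect of height growth since inclusion. Targets are fixed before randomisation, so their expected difference between arms is 0. A between-arm test there should declare non-inferiority about as often as the design power, almost regardless of how fast either arm gains weight.

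**Step 3. Illustration by simulation.** None of the following is in the documents except the 40 per arm, the margin and the BMI distribution, which is borrowed for the targets.
- Target BMI 16.6 ± 1.35; deficit 9 ± 2.5 kg; height 1.40 m; scatter of 0.2 kg/m² at the visit.
- Inpatient gain averages 0.8 kg/week, with a between-child SD of 37.5% of the mean in each arm.
- Only children reaching target within 52 weeks have the visit.
- 4,000 runs per row. Differences are inpatient minus day-patient.

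| Day-patient gain (kg/week) | BMI difference at normalisation | BMI difference at 6 months | Non-inferior at normalisation | Non-inferior at 6 months | Median delay (weeks) | Reach target, IP / DP |
|---|---|---|---|---|---|---|
| 0.8 | 0.00 | 0.00 | 90% | 85% | 0 | 98% / 98% |
| 0.5 | 0.01 | 0.24 | 89% | 57% | 6.8 | 98% / 95% |
| 0.3 | 0.00 | 0.99 | 87% | 3% | 18.9 | 98% / 85% |

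The simulation applies the rate difference from randomisation and has no readmission rule. In the trial the arms share period 1, and failing day patients are readmitted. For a given day-care rate, the delay and the 6-month difference would therefore be smaller than shown. The column at normalisation would still barely move.

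**Step 4. MRS window.** Share before randomisation = (6 − t)/6 for normalisation at month t.
- t = 3: 3/6 = 50%. t = 5: 1/6 = 17%.
- If the score weights the window evenly and the post-randomisation difference is constant, the observed difference is t/6 of the true one: 50% at month 3, 83% at month 5.

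How likely is the overlap? The Procedure section targets 0.5 to 1.5 kg/week. For assumed deficits and a 26-week window:
- 6 kg: 6/1.5 = 4 weeks to 6/0.5 = 12 weeks, so 22 to 14 weeks fall before randomisation.
- 10 kg: 6.7 to 20 weeks, so 19 to 6 weeks fall before randomisation.
- At 0.5 kg/week the window clears randomisation only with a deficit of 26 × 0.5 = 13 kg. With a target BMI of 16.6 and heights of 1.25 to 1.55 m, that means a starting BMI of about 8 to 11.

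Overlap would thus be usual if the targeted gain is sustained. If rates differ, the overlap differs too. A 10 kg deficit takes 10/0.8 = 12.5 weeks or 10/0.5 = 20 weeks, leaving 13.5 or 6 of 26 weeks before randomisation.

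**The case against.** The best case for the plan has five parts.

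**End of treatment is a fair time to look.** Whether children restored to target by day care are as well, psychologically and biologically, as those restored in hospital is a recognisable question, and equal weight is its premise. This stands as a reason to report the visit. It does not make the comparison a randomised one, because it conditions on an event after randomisation.

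**No BMI test with a margin is planned there.** The only stated margin and decision rule concern BMI at 12 months, and the abstract illustrates the clinical secondary outcome by Tanner stage, which is not collected at this visit. This stands in part. Objective 2 nevertheless covers clinical outcomes without exception, and Table 1 lists BMI under clinical assessment at this visit.

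**Unequal timing is not shown.** The Background hopes for comparable weight gain, and the 0.5 to 1.5 kg/week target follows the period 1 description and may not apply to day care. This is correct: the documents support only that timing can differ. They do allow for it, since another objective asks whether the prospect of day care changes the time to stabilisation.

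**Few children may miss the visit.** Treatment and readmission continue until target, and handling of missing data may sit in an SAP not shown. The share may well be small. But an SAP cannot recover a visit whose defining event did not occur.

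**Pre-randomisation recall is balanced by randomisation.** It is, so with equal timing the effect is dilution, not bias between arms. In a non-inferiority comparison dilution is still unhelpful.

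A reader might also infer that the hoped-for social benefit cannot be separated from being in hospital during the recall window. The documents do not support that. Reduced social isolation is what the shorter stay is meant to achieve, so poorer school and social scores during hospitalisation are part of the treatment effect.

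**Conclusion.** The point holds for one of the three time points in objective 2. As written, that objective could produce a non-inferiority statement at a visit where BMI is near-equal by construction, relapse after normalisation cannot yet have occurred, the date depends on treatment, and non-reachers are absent despite the stated ITT analysis. For the MRS, any normalisation before month 6 brings dilution by (6 − t)/6.

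The structural argument rests only on the text. The magnitudes rest on assumed deficits, gain rates and normalisation dates; the documents give neither the timing difference nor the share of non-reachers.

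Two stronger readings should be resisted. Non-inferiority on BMI at this visit is not guaranteed: targets vary between children, and the simulated rate is 87% to 90%, about the design power. Nor is the trial's main conclusion at risk: the primary outcome at 12 months, the sample size and the 6- and 12-month comparisons are unaffected.

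**What to change.** 1. Reword objective 2 so that its non-inferiority comparisons are made at 6 and 12 months, and at 12 months only for nutritional markers, which Table 1 does not schedule at 6 months.
2. Report the weight-normalisation visit, including the MRS, by arm as an end-of-treatment description, with the number reaching the visit and the elapsed time since randomisation.
3. Add time from randomisation to weight normalisation as a secondary outcome, analysed by ITT, with children who do not reach target censored at last follow-up or month 12. Start the clock at randomisation, because stabilisation is itself a post-randomisation event.
4. Keep the 6-month comparison of the MRS and its social subscales. Its window begins at inclusion, and the effect of hospitalisation on social functioning belongs to the treatment effect.

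The cost is the wording of one objective and matching SAP text. No new data are needed, since the date of reaching target already triggers a visit. The downside is that one set of secondary tests becomes descriptive.
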